### Intervention (visit 3)

Treatment will commence within 2 weeks of randomisation at Baseline Assessment.

### 8 Weeks cycling and education programme (CHAIN)

For 8 weeks following randomisation, participants in groups of up to 15, will attend a weekly, one hour education and cycling session at a local leisure centre. Each session will typically involve a 30 min education session which aims to motivate participants to exercise, reassure them that it is safe to do so, and facilitate positive lifestyle/activity change, followed by a 30 min indoor static cycling class (35 and 40 min for the last two sessions). An overview of CHAIN week-by-week is shown in Fig. 2, and a full description of this intervention following TIDIER guidelines [30] can be found in Table 3.

**Fig. 2 Taba:** Overview of the content for the CHAIN intervention, week-by-week

Week	Week 1	Week 2	Week 3	Week 4	Week 5	Week 6	Week 7	Week 8
Education session (30 min)	Introduction	Review of last session	Review of last session and activity diary	Review of last session and activity diary	Review of last session and activity diary	Review of last session and activity diary	Review of last session and activity diary	Review of last session and activity diary
	Aims of programme	Introduction to activity diary	Complementary therapies	Pacing	Nutraceuticals and supplements	Oral analgesics	Self-management tips and planning	Summary of previous sessions
	Introduction to osteoarthritis (OA) and the hip joint	Introduction to Home Exercise Programme (HEP)	Assistive devices and footwear	Manual therapy, manipulation and stretching	Alternative exercise options	Topical treatments	Injections and surgical options Part I	Injections and surgical options Part II
	Benefits of exercise for OA Part I	Benefits of exercise for OA Part II	Diet, nutrition and weight loss	Thermotherapy	Electrotherapy and acupuncture	Non-steroidal anti-inflammatory drugs (NSAIDs)	Post programme exercise planning	Post programme exercise and support networks
	Cycling technique Part I	Cycling technique Part II	Cycling technique Part III	Cycling technique Part IV	Cycling technique Part V	Cycling technique Part VI	Cycling technique Part VII	Cycling technique revision
Static Cycling Session	30 min	30 min	30 min	30 min	30 min	30 min	35 min	40 min
Home Exercise Programme (HEP)	Daily HEP 2 × 30 min cycling per week	Daily HEP 2 × 30 min cycling per week	Daily HEP 2 × 30 min cycling per week	Daily HEP 2 × 30 min cycling per week	Daily HEP 2 × 30 min cycling per week	Daily HEP 2 × 30 min cycling per week	Daily HEP 2 × 30 min cycling per week	Daily HEP 2 × 30 min cycling per week

**Table 3 Tab3:** CHAIN Intervention description following the TIDIER checklist [24]

1. Name	CHAIN: Cycling against Hip Pain
2. Why	The rationale for the CHAIN intervention is based on the need to develop an effective model of care locally to deliver the nonsurgical interventions recommended by NICE (2014). It was conceived by a consultant orthopaedic surgeon and a physiotherapist in response to discussions locally with primary care providers suggesting that ‘standard care’ for patients reporting hip stiffness to their GP can be varied and inconsistent, ranging from general advice, advice on analgesia and/or physiotherapy and self -management. It was further developed through discussion with local orthopaedic teams and physiotherapists and in partnership with the local general hospital, the county commissioning group, general practitioner localities, the county sports partnership, the borough council and the university. The aim of the programme is to reduce pain and encourage mobility through a programme of education and static cycling sessions to equip participants with the confidence to self-manage their condition.
3. What: Materials	CHAIN videos which will be shown to participants by the facilitator during the CHAIN sessions and can be accessed by the participants in their own time after the sessions. The cycling sessions were developed by senior physiotherapist and fitness instructors from the leisure centre to ensure that the sessions are the same in each cohort. Figure 2 shows a breakdown of the cycling and education content week-by-week.
4. What: Procedures	**Screening**: Prior to enrolment, participants are reviewed under the GP referral for exercise to ensure their suitability to attend the sessions. **Education**: For the first thirty minutes, participants will take part in an education class, facilitated by a qualified physiotherapist. The education sessions will be standardised through video recordings developed by the study team and based upon NICE guidelines, aiming to promote the effective on-going self-management of hip pain. The education classes also aim to motivate participants to exercise, reassure them that it is safe to do so, and facilitate positive lifestyle/activity change. At the end of the class, the physiotherapist will encourage group discussion so that participants can share their questions and experiences. **Cycling**: The education session will be followed by a 30 min indoor static cycling class (35 and 40 min for the last two sessions respectively), facilitated by a gym instructor trained in leading indoor cycling classes. On the first week, participants will be shown how to set up their bike. The intensity of the exercise class will increase on a weekly basis and will be clearly defined to ensure each cohort will be given the same programme. Each session will finish with a cool-down period which will include relevant stretches. Participants will be encouraged to work at a level that they are comfortable with and will be encouraged to increase their intensity progressively over the eight sessions. **Between sessions**: After completion of the class, the participants will receive a video of the education class and of the static cycling session, via text or email, to encourage exercise and compliance to behaviour change advice at home. A home exercise programme comprising of various ankle, knee and hip stretches will also be provided and participants will be encouraged to stretch regularly. Cycling between sessions will be encouraged but will not be mandatory. To encourage participants to increase their exercise activities, an activity diary will be provided so that progress at home can be recorded and monitored for the duration of the intervention, including planned pauses in the delivery of the intervention. Plans for lifestyle changes and on-going participation in community-based activities will also be discussed.
5. Who provided	**Physiotherapists**: Local NHS senior physiotherapists will facilitate group discussions during each weekly education session. As trained by the study team, they will encourage participants to share experiences and ask questions related to that week’s topic or the management of their hip pain in general. The physiotherapists will also ensure adherence to the intervention by reminding participants to complete their activity diaries in between sessions. **Fitness Instructor**: a qualified and experienced fitness instructor from the local leisure centre will deliver the cycling session each week. The fitness instructors have experience of leading cycling sessions with mixed ability groups and have helped to design the content of each weeks’ session alongside the study team.
6. How	The intervention will be delivered face-to-face in a group setting. After each weeks’ session, participants will be sent a link (via email or text message) to that weeks’ education and cycling session as well as the home exercise programme so that they can be reviewed in between sessions in participants’ own time. A short report detailing changes in assessment scores will be sent to participants following treatment.
7. Where	Intervention will be delivered at a suitable local leisure centre, equipped with space to deliver the education session and an appropriately equipped cycling studio that has space for up to 15 participants to take part in a single cycling session
8. When and how much	The CHAIN intervention is an 8-weeks cycling and education programme where participants will attend a one-hour education and exercise session on a weekly basis at a local leisure centre. It is not necessary for the intervention to be delivered in consecutive weeks and a short pause in delivery of the programme will be possible in the case of local facilities having to close, i.e., due to public holidays or other situations out of the study team’s control. However, if a participant misses a planned course, there will not be an opportunity to provide a catch-up session and the participant will be marked as absent from the session. Dosage received for each participant will be calculated based on sessions attended and length of those cycling sessions along with the recommended cycling intensity.
9. Tailoring	Static cycling is an accessible form of exercise which can be tailored to all levels of ability and fitness within a group setting.
10. Modifications	N/A
11. How well: Planned	Adherence will be assessed by registering the attendance of each participant at each session. Activity diaries will be given to participants to record any activities undertaken outside of the intervention. Participants will be reminded by the senior physiotherapist each week of the importance of the completion of these diaries including recording of the how frequently participants complete the Home Exercise Programme (HEP). The activity diaries will be collected at the Visit 4 and the data analysed, including adherence to the HEP
12. How well: Actual	N/A

### Control arm: standard physiotherapy care

The Trust Physiotherapy Department will allocate treatment slots (within two weeks of randomisation) for participants in the control arm. Once randomised to this arm, at their baseline visit participants are given the next available date and time for their first treatment session. Thereafter the physiotherapy appointments are made between the participant and the Physiotherapy Department directly as per standard care. Over 8 weeks, participants in the control group will attend up to four one-to-one sessions of physiotherapy (as per NHS standard care [27]) for up to two hours. These visits may be face-to-face at the Trust Physiotherapy Department or by telephone depending on the physiotherapist’s standard care practice at the time of treatment. Treatment will be pragmatic and multimodal and may include exercise, education, manual therapy, and other physiotherapy techniques. Participants will also be encouraged to complete a series of home exercises as prescribed by their physiotherapist. The exact treatment received, and the duration and number of sessions delivered will be recorded by the physiotherapist providing the treatment in patient notes and the study proforma (Supplementary File 4). This will enable the dosage of the intervention (type, intensity, and time) for participants in the control arm to be compared to that received by participants in the CHAIN arm. This arm will also complete activity diaries to record activities undertaken outside the physiotherapy sessions and physiotherapists will remind participants of their completion. It will be collected at the post-treatment Visit 4. In instances where it is not possible for the physiotherapy department to conduct all the required appointments within the 8 weeks treatment period (e.g. due to illness or capacity issues) an extension to complete appointments will be possible. However, participants will continue to be assessed within two weeks of the allocated 8-weeks study treatment period, and again 3 months later as per the protocol. Any treatment in the control arm outside of the 8 weeks period will be recorded as such.

### Follow-up (visit 4, visit 5)

There will be two follow up assessments, the first within 2 weeks of the end of the CHAIN intervention (or end of 8 weeks treatment period for the control arm) (Visit 4) and the second (Visit 5) occurring approximately 3 months after the post-treatment visit. Visit 4 will be undertaken by trained, qualified physiotherapists and will consist of the same physical and functional assessments performed at Visit 2, completion of patient questionnaires as well as a review of participants’ activity diaries and a feedback questionnaire for those participants that were randomised to the CHAIN intervention; Visit 5 consists of 5 patient questionnaires (Hip Disability and Osteoarthritis Outcome Score (HOOS); Patient Specific Functional Scale (PSFS); Patient Activation Measure (PAM); EQ-5D-5 L; and resource use) sent to participants by email or post. Participants will be contacted by text/telephone/email to help ensure completion and return of questionnaires. Where this is difficult to achieve, we will prioritise collection of the primary outcome at Visit 4. The data to be collected at each of these follow-up appointments are summarised in Table 1.

### Outcomes

#### Primary outcome

The primary outcome is the function, daily living component from the Hip Disability and Osteoarthritis Outcome Scale (HOOS) [25], measured at Visit 2 and Visit 4.

#### Secondary outcomes

We are measuring a number of secondary outcomes including participant reported outcome measures, resource use and QALYs at both Visit 4 and visit 5; and changes in physical and functional measurements at Visit 4. These are summarised in the SPIRIT diagram (Table 1), but in brief are as follows:

HOOS function, daily living score measured out of 100, after completion of the HOOS Questionnaire at Visit 2 and Visit 5 (score at Visit 4 is primary outcome);HOOS pain score measured at Visits 2, 4 and 5; HOOS symptoms score measured at Visits 2, 4 and 5;HOOS stiffness score measured at Visits 2, 4 and 5;HOOS sports and recreational activities score measured at Visits 2, 4 and 5;HOOS Quality of Life score measured at Visits 2, 4 and 5;Function assessed by 30-second chair stand test measured at Visit 2 and 4;Function assessed by stair climb test measured at Visit 2 and 4;Function assessed by 40-metre walk test measured at Visit 2 and 4;Patient activation measured by responses to PAM Questionnaire at Visits 2, 4 and 5;BMI, body composition, blood pressure and resting heart rate measured at Visits 2 and 4;Analgesia use collected from the Resource Use Questionnaire during Visits 2, 4 and 5;Patient-perceived general health measured using EQ-5D Visual Analogue Score (VAS) at Visits 2, 4 and 5;Patient-perceived quality of life measured by EQ-5D-5 L Questionnaire at Visits 2, 4 and 5, used to derive Quality Adjusted Life Years (QALYs).Self-reported resource use measured by responses to the Resource Use Questionnaire during Visits 2, 4 and 5.

### Adverse events

Hip OA is a non-life-threatening condition typified by on-going progression of symptoms and deterioration of function. From the time the participant signs the consent form until the day the participant has completed their post-treatment assessment (Visit 4), the only adverse events recorded will be those for which participants seek advice from a health care professional, such as an unplanned visit to a General Practitioner for an acute condition. Participants will be asked at the start of each CHAIN session or physiotherapy session whether they have had any adverse events, and they will be asked again at the assessment post-treatment.

Based on our feasibility study [18] as well as a case study of a participant with a number of co-morbidities [26], the intervention is deemed low risk. Therefore, we are not expecting any serious adverse events.

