A review of potential mechanisms underpinning the benefits of exercise therapy on pain and function in OA found that an increase in upper leg strength, a decrease of extension impairments, and an improvement in proprioception, were all possible mediators of the link between exercise and a decrease in OA symptoms in the lower limb; another review highlighted the need to address muscle weakness in people with hip OA [12, 13]. Cycling has been found to improve balance and proprioception, induce muscle hypertrophy, directly improve muscle weakness and therefore upper leg strength, and (because it is non-weight-bearing) causes less stress on the joints than running or other impact sport [14–16]. Additionally, longitudinal epidemiological studies [17] have shown that cycling can increase cardiorespiratory fitness and functional ability, and lead to significant risk reduction for all-cause and cancer mortality, cardiovascular disease, colon and breast cancer, and obesity morbidity in the middle-aged and elderly.

As a way of implementing the NICE guidelines for hip OA, a cycling and education intervention, the CHAIN (Cycling against Hip pAIN) programme, was developed in 2013 through discussions with local orthopaedic teams and physiotherapists [18] and was updated following feedback from past CHAIN participants. The CHAIN intervention aims to equip participants with the confidence to self-manage their condition, to encourage joint mobility and reduce pain through an 8-week programme of education and static cycling sessions [18–20]. The intervention has been designed to influence behaviour change and includes components to motivate, increase adherence, and reduce drop-out of participants.

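### Adverse events are recorded only if the participant sought professional advice, so equal harm can give unequal counts by arm, in a direction the protocol does not fix

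*Protocol article*

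**What the plan says.** The recording rule is in the protocol article, Adverse events. It applies from consent up to Visit 4, and states that "the only adverse events recorded will be those for which participants seek advice from a health care professional". The one example of a qualifying contact is given as "such as an unplanned visit to a General Practitioner for an acute condition". On how events come to light, the section says: "Participants will be asked at the start of each CHAIN session or physiotherapy session whether they have had any adverse events". The question is put again at the post-treatment assessment. The section gives as context that "Hip OA is a non-life-threatening condition typified by on-going progression of symptoms and deterioration of function", and it calls the intervention low risk.

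Other sections bear on who seeks advice and who is asked:

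- Background: "The CHAIN intervention aims to equip participants with the confidence to self-manage their condition".
- Table 3, item 4, describes the standardised education sessions as "aiming to promote the effective on-going self-management of hip pain". Fig. 2 lists pacing, oral analgesics, topical treatments and self-management tips among the topics.
- Table 3, item 5: a senior NHS physiotherapist leads the discussion at each weekly CHAIN session and invites questions about managing hip pain.
- Control arm: over 8 weeks "participants in the control group will attend up to four one-to-one sessions of physiotherapy". Some may be by telephone, and the content may include education.
- Abstract, Methods: contacts with primary and secondary care are part of a secondary outcome.
- Randomisation: participants and treatment providers are not blinded.

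**The concern.** The rule defines a recordable harm by the participant's response to it, not by the event. A flare that the participant treats with analgesia, or by resting and missing a class, does not qualify, however often the participant is asked about it. This is the most foreseeable harm of a programme whose intensity rises weekly.

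The trial treats professional contact as something that may differ between arms, and uses the same contact to decide what counts as a harm. If an arm changes how often people consult, its recorded harms change with no change in safety. A second source of imbalance is that CHAIN participants meet a physiotherapist, and are asked about adverse events, about twice as often.

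At stake is the reading of the harms table. A lower or higher count in one arm could reflect consulting habits or opportunity to report. A later analysis plan cannot repair this, because events that were never recorded cannot be analysed.

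**Working it through.** **Figures in the plan.** The Adverse events section states no flare, care-seeking or disclosure rate, so it has no figure to reproduce. Two figures are taken from Sample size calculation. The target reproduces: 102/(1 − 0.20) = 127.5, so 128 per arm and 256 in all. The 7.4 HOOS points for 5 WOMAC points is consistent with the stated standard deviations: 7.4/5 = 1.48 and 19.1/13 = 1.47, equal within rounding.

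**Assumed inputs.** Flare rate f, the same in both arms; probability s that a control flare leads to advice; ratio r of CHAIN's care-seeking probability to control's; probability q of disclosure per enquiry. None is in the documents.

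**Step 1, care-seeking alone.** Expected recorded events per arm = 128 × f × s in control and 128 × f × s × r in CHAIN.

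| f | s | Control | CHAIN, r = 1 | r = 0.8 | r = 0.6 |
|---|---|---|---|---|---|
| 40% | 50% | 25.6 | 25.6 | 20.5 | 15.4 |
| 20% | 30% | 7.7 | 7.7 | 6.1 | 4.6 |

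A real excess can also be hidden. With flares in 26% of CHAIN and 20% of control, and care-seeking of 35% and 50%, the recorded rates are 26% × 0.35 = 9.1% and 20% × 0.50 = 10.0%. With equal flares of 20% and care-seeking of 60% and 50%, CHAIN looks worse: 12.0% against 10.0%.

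**Step 2, enquiry alone.** Under full attendance CHAIN has 8 + 1 = 9 enquiries and control at most 4 + 1 = 5. Captured share c = 1 − (1 − q)^k for k enquiries. This treats each event as open to disclosure at every enquiry, independently, which is a simplification.

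**Step 3, both together.** Recorded ratio CHAIN/control = r × c(9)/c(5). CHAIN records fewer events only if r is below the break-even value c(5)/c(9).

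| q | c(9) | c(5) | Ratio, r = 1 | r = 0.8 | r = 0.6 | Break-even r |
|---|---|---|---|---|---|---|
| 0.2 | 86.6% | 67.2% | 1.29 | 1.03 | 0.77 | 0.78 |
| 0.3 | 96.0% | 83.2% | 1.15 | 0.92 | 0.69 | 0.87 |
| 0.5 | 99.8% | 96.9% | 1.03 | 0.82 | 0.62 | 0.97 |

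If control participants have only two sessions (k = 3), the captured shares are 48.8%, 65.7% and 87.5%, and the break-even values fall to 0.56, 0.69 and 0.88.

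With no true difference in harm, the recorded ratio therefore falls on either side of 1, depending on quantities the documents do not give.

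**The case against.** A reader might infer that the rule favours CHAIN: teach people to manage their own flares and they take fewer to a professional. The documents do not support that as a net conclusion. No section says that CHAIN aims to reduce advice-seeking; this is inferred from the self-management aim. The sessions also cover analgesics, injections and surgery, which could prompt consultations. Control care may include education too. CHAIN participants see a physiotherapist weekly and are invited to raise hip pain. If telling that physiotherapist counts as seeking advice, CHAIN could be over-recorded. The article does not say whether it counts, although a condensed article may leave that detail to the full protocol.

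It can also be said that the rule is a reasonable severity threshold for a low-risk intervention in a progressive condition. Adverse events sit under other measures in Table 1, and no between-arm test is stated. HOOS pain, analgesia use, attendance and diaries capture part of the same experience without needing a consultation. Serious events would normally reach a professional anyway (an assumption), so the effect falls mainly on minor events.

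These points settle the direction question against the stronger reading and limit the importance of the issue. They do not rescue the rule. Frequent asking does not help an event that fails the definition, and nothing suggests that the two sources of imbalance cancel. The other measures are useful supplements but are not adverse-event records.

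**Conclusion.** The concern holds in a limited form. Adverse-event recording depends on a post-randomisation behaviour that may differ by arm, and the number of enquiries is unequal, so recorded counts cannot be read as a clean comparison of harm. The direction and size of the bias are unknown. The range of 0.62 to 1.29 in the recorded ratio under equal harm rests wholly on the assumed values of r and q, with full attendance and four control sessions; it illustrates that the sign is open and is not an estimate. The primary outcome and the sample size are unaffected.

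**What to change.** In both arms, record every new or worsened symptom disclosed at the enquiries already scheduled. Enter professional contact, and whether it was with the treating physiotherapist or someone else, as an attribute of the event and not as the condition for recording it. Triggers such as missed sessions or changed analgesia should not replace the present condition: CHAIN has more sessions to miss and teaches about analgesics, so these also depend on arm.

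Base the between-arm comparison on the one enquiry common to both arms, at Visit 4 and covering the whole treatment period. Report events disclosed at sessions separately.

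For participants already followed under the present rule, report counts by rule version and state that the arm comparison depends on care-seeking.

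Add a table by arm of the proportion whose HOOS function, daily living score is worse at Visit 4 than at baseline by at least 7.4 points, the trial's own figure for that subscale. Describe HOOS pain change by arm without borrowing that threshold, which was derived for function.

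The cost is a reworded sentence, a revised form and one descriptive table from data already collected. More minor events will be recorded. Trial status gives recruitment as due to finish by May 2023, so a late change leaves two recording rules within the trial, and earlier unrecorded events cannot be reliably recovered. The table compares two time points and would miss transient flares.

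### Adverse events are asked about at treatment sessions, up to 9 times in CHAIN and at most 5 in control, so any summary of harms by arm rests on unequal ascertainment

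*Protocol article*

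**What the plan says.** The Adverse events section of the protocol article sets the enquiry schedule: "Participants will be asked at the start of each CHAIN session or physiotherapy session whether they have had any adverse events". A final enquiry follows for everyone at Visit 4, in both arms: "they will be asked again at the assessment post-treatment". Recording starts when consent is signed and runs "until the day the participant has completed their post-treatment assessment (Visit 4"). Only events that led the participant to consult a health professional are recorded. Table 1 ticks adverse events at baseline, treatment and post-treatment, but not at Visit 5.

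The number of sessions differs by arm:

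- **CHAIN** (section on the 8-week programme): "participants in groups of up to 15, will attend a weekly, one hour education and cycling session at a local leisure centre", for eight weeks. Under item 8 of Table 3, if a session is missed "there will not be an opportunity to provide a catch-up session", so eight is a ceiling. The same item allows a short pause in delivery.
- **Control** (section on standard physiotherapy care): "participants in the control group will attend up to four one-to-one sessions of physiotherapy". If the department cannot complete the appointments in eight weeks, "an extension to complete appointments will be possible". The date of Visit 4 does not move with such an extension: "participants will continue to be assessed within two weeks of the allocated 8-weeks study treatment period".

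The Follow-up section anchors Visit 4 to the end of the CHAIN programme in one arm and to the end of the 8-week period in the other.

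**The concern.** How often a participant is asked about harms depends on the allocated arm. If repeated asking picks up events that a single later question would miss, CHAIN will show more events even when the true rates are equal. A CHAIN window lengthened by a pause works in the same direction, because it adds weeks in which events can occur and be recorded.

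The article supports its view that the intervention is low risk with a feasibility study and a case study. This trial is the chance to look at harms under randomisation. It is to be reported according to CONSORT, so a reader will see events by arm. A small excess in CHAIN could then partly reflect detection, and a small advantage for CHAIN could be hidden. The schedule is part of data collection and is stated in the article; it is not a detail left to the analysis plan.

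**Working it through.** The article gives no count of enquiries per arm, so there is no stated figure to reproduce. The counts follow from its session numbers.

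**Step 1: number of enquiries after randomisation** (sessions + 1 for Visit 4)

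- CHAIN: 8 + 1 = 9 at most.
- Control: 4 + 1 = 5 at most.
- Ratio of enquiries: 9/5 = 1.8. Counting the baseline tick in Table 1 gives 10 and 6, a ratio of 1.67.

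**Step 2: what this could do to recorded events**

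The article gives no detection probability, so the following are assumptions: equal true event rates; events uniform over 10 weeks; Visit 4 at week 10 in both arms; each enquiry after an event picks it up independently with probability d. An event followed by k enquiries is recorded with probability 1 − (1 − d)^k. Averaging over event times gives the proportion recorded.

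Enquiry times in weeks: CHAIN 1 to 8 and 10; control with four sessions 1, 3, 5, 7 and 10; control with two sessions in the window 1, 5 and 10.

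Worked case, d = 0.5. The proportion missed is the sum of (interval length × 0.5^k), divided by 10:

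- CHAIN: eight one-week intervals with k = 9 down to 2 contribute 0.498, and the last two weeks with k = 1 contribute 2 × 0.5 = 1. Missed 1.498/10 = 0.150; recorded 0.850.
- Control, four sessions: 0.031 + 2(0.0625) + 2(0.125) + 2(0.25) + 3(0.5) = 2.406. Missed 0.241; recorded 0.759. Ratio 0.850/0.759 = 1.12.
- Control, two sessions: 0.125 + 4(0.25) + 5(0.5) = 3.625. Missed 0.3625; recorded 0.638. Ratio 0.850/0.638 = 1.33.

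All cases, as proportion recorded and ratio of CHAIN to control:

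| d | CHAIN | Control, 4 sessions | Ratio | Control, 2 sessions | Ratio |
|---|---|---|---|---|---|
| 0.5 | 0.850 | 0.759 | 1.12 | 0.638 | 1.33 |
| 0.7 | 0.927 | 0.885 | 1.05 | 0.811 | 1.14 |
| 0.9 | 0.979 | 0.968 | 1.01 | 0.946 | 1.04 (1.035 before rounding) |
| 1.0 | 1.000 | 1.000 | 1.00 | 1.000 | 1.00 |

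**Step 3: the recording window**

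The table holds the window equal. The article does not give the length of a pause. If Visit 4 would otherwise fall at week 10, an assumed one-week pause in CHAIN makes the window 11 weeks against 10, or 11/10 = 1.10 times the recording time. An analysis per person-week removes this part.

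For control treatment extended past eight weeks, Visit 4 does not move and recording ends there. The late treatment itself is documented, but no adverse-event collection is described for it.

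**The case against.** The strongest case against is that the article promises no between-arm comparison of harms. Adverse events are listed under other measures in Table 1, are not among the secondary outcomes, and are not mentioned in the Statistical analysis section. Asking at each treatment contact is ordinary safety monitoring. Both arms get the same closing question at Visit 4, and the Resource Use Questionnaire collects health-care contacts on the same schedule in both. An event serious enough to prompt a consultation is likely to be remembered over some ten weeks.

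Much of this stands, and it limits the weight of the point. It does not remove it, because events shown by arm would still carry the unequal schedule, whether or not they are tested. The recall argument also has a gap: the article does not say whether raising a problem with the physiotherapist at a session counts as seeking advice.

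On timing, the sentence in Aim and objectives that dates follow-up from completion of CHAIN could be read as applying to both arms. The Follow-up and control-arm sections give the control arm its own anchor, so the unequal window is the better-supported reading.

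A reader might infer three stronger things that the article does not support:

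- **That CHAIN events will be inflated 1.8-fold or more.** That is a ratio of questions. A ratio of 4.5 arises only by setting full CHAIN attendance (9) against a control with a single session (2), and the article does not say how often that happens.
- **That detection could not be separated from harm.** The Visit 4 question and the questionnaire are common to both arms and provide a check.
- **That ending recording at Visit 4 is itself unequal.** The cut-off applies to both arms, and holding control Visit 4 in place keeps its follow-up time regular. What is lost is cover of late control treatment.

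**Conclusion.** The point holds in limited form. The enquiry schedule differs by arm, up to 9 against at most 5, and the CHAIN recording window can lengthen with the programme while the control window does not. The likely effect is a modest excess of recorded CHAIN events, about 1.0 to 1.3-fold. The upper end needs half of the events to be missed at each enquiry and only two control sessions before Visit 4; with four control sessions the range is 1.00 to 1.12. These figures rest on the assumptions in the working, not on data in the article, and they exclude any difference in window length. The consequence is confined to descriptive safety reporting; the primary outcome and its analysis are untouched. The change is worth making because it is cheap.

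**What to change.** 1. At Visit 4, put the same structured adverse-event question to both arms, covering the whole period since randomisation.
2. Cross-check the answers with the health-care contacts in the Visit 4 Resource Use Questionnaire.
3. Base any between-arm summary of harms on these two sources, over a common window from randomisation, or express it per person-week.
4. Keep the session-by-session questions for safety oversight. Show those events separately, labelled as unequally ascertained.
5. State as a limitation that events during control treatment extended beyond Visit 4 are not captured. Steps 1 to 4 do not solve this.

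The cost is protocol and analysis wording; a Visit 4 enquiry and the questionnaire already exist in both arms. The form must show whether an event was reported at a session or at Visit 4. Recruitment is under way, so a reworded question reaches only participants not yet assessed. The downside is longer recall for the comparative summary, equal in both arms if the window is the same.
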